### Digital support system

All users had access to a digital support system in the form of a web page with a common database and specific user interfaces for the GP, the municipality health professionals, and the patient. No apps were developed. The system design drew inspiration from the work by Krist and colleagues’ research on preventive EPRs, and was further inspired by the results of a Delphi process carried out to identify factors for optimal development of health-related websites [34–36]. Due to challenges in terms of interoperability between the eight suppliers of EPR systems used by GPs, and at least three suppliers of electronic care records (ECR) in the municipalities, it was not feasible to develop a support system that completely integrated the EPR and ECR systems. Instead, the digital support system was developed as a parallel system with an additional functionality facilitating the transfer of information (e.g. relating to lifestyle and/or prevention plans) to the EPR and ECR systems using Electronic Data Interchange (EDIfact) messages [22]. The patient controlled access to personal health information on the system, such that the GP and municipal health professional were only able to access this information with the explicit consent of the patient.

The digital support system was developed iteratively in collaboration with the users during the before mentioned workshops with municipality health professionals and GPs and in the form of usability tests with patients. The user interface for the patient was responsive and compatible with most devices, including mobile phones, tablets, laptops and stationary computers. Due to technical constraints in the secure log-in provided by NemID, the user interface for health professionals was only developed for laptops and stationary computers. In order to make the user interface for the patient as intuitive and user-friendly as possible, the digital support system made extensive use of simple visualizations, icons, and short information videos (Fig. 1). The primary text-based messages were kept short and concise with the provided possibility of accessing secondary in-depth information, retrieved from the Danish Health Portal, sundhed.dk [37].

**Fig. 1 Fig1:**
[figure not shown]
Screen dump from digital support system (in Danish)

Beyond facilitating the intervention, the digital support system also enabled data collection for research purposes. A number of questionnaires were sent from the digital support system to the participants at specific time-points, including immediately after consent, after receiving the personal health profile, following the health dialogue at the GP, and at the end of the implementation period. Questionnaire reminders were sent by e-mail with a link to the digital support system. The GPs and municipal health professionals received audits in the form of short questionnaires immediately after each consultation as well as before and after the study period (GPs only).

### Personal health profile

Based on results of the stratification process, each patient received a personal health profile on the digital support system. The purpose of the health profile was to encourage patients to change their health-risk behavior and follow the tailored advice provided by the system. Patients who were at increased risk of developing a lifestyle-related disease (Group 2) were advised to consult their GP for further examination and advice. Similarly, patients engaging in health-risk behavior (Group 3) were offered lifestyle counseling, or lifestyle courses from the municipality health services. By definition, Group 4 patients lead a relatively healthy life with no need for health-risk behavior change. Group 1 patients were advised to continue their treatment and use the information provided to change health-risk behavior.

The personal health profile included individualized information on current health-risk behavior and risk of disease. The information was tailored based on the questionnaire, the information from the EPR, and the risk scores on COPD, T2DM, and CVD. It also included general health information and information about preventive health services concerning smoking, diet, exercise, and alcohol consumption. This information was provided by the municipality, the Region of Southern Denmark, or national health services, and targeted the individual (e.g. via links to apps and webpages) based on his/her specific health-risk behavior.

### The targeted intervention

#### The intervention at the GP

The intervention at the general practice level consisted of a focused clinical examination and a subsequent health dialogue and was offered to patients who were at increased risk of developing a lifestyle-related disease (Group 2). Group 2 patients accepted the offer of the intervention by scheduling an appointment at the GP (either by phone or the GP’s webpage). Whether the patient participated in the intervention or not was thus determined by their motivation and capabilities as well as the extent to which the content of the personal health profile motivated the patient to take action. The intervention was applied within the framework of the 5As model (see Table 1) [28]. The content of the focused clinical examination was based on the patient’s health profile, and might include measurements of blood glucose (HbA1c) and cholesterol levels, as well as height, weight, blood pressure, and lung function measurements and Electrocardiogram (ECG). Results from the examinations were registered in the digital support system where both the patient and the GP could access them at any time. After the focused clinical examination all patients were given the opportunity to prepare for the subsequent health dialogue by answering a questionnaire inspired by three systematic reviews on the determinants of behavior change [38–40]. These included questions about motivation, resources, former experiences with behavior change, social network, mental health (WHO-5 for stress and Major Depression Inventory (MDI) for depression) [41, 42], and a scheme to qualitatively self-report on facilitators and barriers to behavior change (a so-called balance-sheet). The questionnaire results were shared with the GP on the digital support system. Based on the health dialogue, the GP and the patient developed a prevention plan that included a goal, a time frame, and identification of the appropriate means to fulfill the plan (e.g. reference to a smoking cessation course, or follow-up at the GP). The prevention plan was registered on the digital support system by the GP and was accessible to both the GP and the patient.

#### The intervention at the municipal level

The intervention at the municipal level was offered to patients exhibiting health-risk behavior (Group 3) and consisted of a short telephone consultation with a health professional – for example a nurse, a dietician, or a physiotherapist. A subsequent face-to-face health dialogue was offered to patients who were deemed to potentially benefit from more extensive support. Group 3 patients requested the intervention on the digital support system by filling in a short form and sending it by e-mail to the municipality. A municipal health professional would then call the patient within the following week. Similar to the GP intervention, the intervention at the municipal level was thus also determined by patient motivation and capabilities as well as the extent to which the content of the personal health profile motivated the patient to take action. Immediately after the intervention, a participation form was sent to the municipality. Patients could prepare for the upcoming call from a municipal health professional in the same way as Group 2 patients prepared for the health dialogue – that is, by answering a short questionnaire. Ultimately, a prevention plan, including concrete details on its execution, was developed based on the telephone consultation and the face-to-face health dialogue. The prevention plan was registered by the municipal health professional and presented on the user interfaces of both the municipality and the patient.

### Sample size calculation

While aiming to test the acceptability, feasibility, and short-term effects of the pilot, we estimated a sample size for each GP that would allow the GP to familiarize him/herself with the intervention without unnecessary increases in workload during the intervention period. In agreement with the GP representative in the Region of Southern Denmark, we set a target of four health checks for each GP. From the feasibility study, we estimated that 60% would consent to the study, and that 75% of these participants would receive a personal digital health profile [22]. Also based on the feasibility study, we estimated that 12% of the study population would be recommended to consult their GP (Group 2). From results obtained in similar Dutch studies, we finally estimated that 35% of the these patients (Group 2) would eventually consult the GP [43]. Given these figures, we calculated that a total sample of approximately 200 patients from each GP would be required to reach the target of four completed health checks per GP.

### Data collection and analysis

#### Evaluation outcomes

Evaluation of the study will be carried out using quantitative as well as qualitative research methods (Table 6). All outcome measures are based on validated instruments and aim to provide results pertaining to intervention acceptability, feasibility, and short-term effects. In addition, outcomes related to other associated topics will be included. The specific instruments used will be described in detail in later publications.

**Table 6 Tab6:** Outcomes

Outcome	Data input
Change in proportion of patients at increased risk of lifestyle related disease from baseline to the 12 weeks follow up	Questionnaire at baseline (Q2) and end of study period (Q6 and Q7). Risk of lifestyle related disease is based on the algorithms previously described in the methods section and in Tables 3, 4 and 5
Determinants of participation and non-participation	Questionnaire at baseline (Q2). Participants and non-participants will be compared with regard to socio-demographic characteristics, morbidity and contextual characteristics
Evaluation of the digital support system with focus on design, usability and effect of the decision support system	Focus group interviews before study start comprising 6 GPs, 6 practice staff members, 6 municipality staff members, 6–8 patients and representatives from 6 to 8 stakeholder organizations, respectively
	Qualitative interviews with 8–10 patients before and after the health dialogue at the GP, and qualitative interviews with 6–8 GPs after health dialogues, focusing on the experienced usefulness of the digital support system
	Questionnaire to all participating patients immediately after signing the consent form (Q1) and after receiving the health profile (Q3 and Q4) and to all participating GPs and municipality staff members following each study related patient encounter (Q8-Q13)
Process evaluation focusing on the intervention in general practice and the municipality	Participant observation of 10–15 health dialogues in different general practices, followed by qualitative interviews with the participating patients, GPs and practice staff
	Focus group interviews with 6–8 municipality staff members involved in the study and interviews with 10–15 patients who have attended a health dialogue in the municipality
	Questionnaire to all participating GPs, practice staff members and municipality staff members following each study related patient encounter (Q8-Q13)
Process evaluation focusing on the organizational basis of the pilot implementation	Interviews with stakeholders involved in the planning, implementation and evaluation of the study; GPs, practice staff members, municipality staff members, patients, project leaders, researchers
Process evaluation focusing on the common training course for enrolled GPs, practice staff and health professionals from the municipalities	Interviews with GPs and municipal health professionals and questionnaire at the end of the course
GP and patients preferences with regard to the content of the health dialogue, and change in preferences during the study period	Questionnaire using discrete choice modelling (Q4, Q7, Q8, Q11)
Patients’ perceptions of relational empathy following the health dialogue at the GP	Questionnaire including The Consultation And Relational Empathy (CARE) measure following each behavior counseling session in general practice (Q5)
Quality of Life Subscale on the Hip injury and Osteoarthritis Outcome Score (HOOS)/Knee Injury and Osteoarthritis Outcome Score (KOOS)	Questionnaire at baseline (Q2). Participants replying “yes” to any of the osteoarthritis related questions on hip/knee pain, GP care seeking or surgery at baseline will receive additional questions on knee/hip related quality of life and mechanical alignment of the leg and foot [55]
Patient enablement following the health dialogue at the GP	Questionnaire with Patient Enablement Instrument (PEI) (Q5)
Patient reported 1. Meaning-Making and Health, 2. Spiritual Wellbeing, 3. Religious belief and practices	Questionnaire items are sampled from the validated questionnaire SoMe (Sources of Meaning) and European Value Study (EVS) (Q6 and Q7)
GP reported 1. Perceived importance of communication on existential and spiritual issues, 2. Self-efficacy and barriers in communication on existential and spiritual issues, 3. Personal belief	Questionnaire items sampled from the validated Self-efficacy questionnaire, European Value Study (EVS) and two items developed for this study evaluation (Q6 and Q7)
Patient reported self-efficacy and change in self-efficacy during the study period as a result of participation	Questionnaire incl. The General Self-Efficacy Scale (Q3, Q4, Q6 and Q7)
Patient reported mental well-being and change in mental well-being during the study period as a result of participation	Questionnaire incl. The Warwick-Edinburgh Mental Well-being Scale (WEMWBS) (Q3, Q4, Q6 and Q7)

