COPD	R95	or	R03AC18 (indacaterol), R03AC19 (Olodaterol), R03AL03 (vilanterol), R03AL04 (Indacaterol+Glycopyrroniumbromide), R03AL05 (Formoterol+Aclidiniumbromide) R03BB04 (tiotropium bromide), R03BB05 (Aclidiniumbromide), R03BB06 (Glycopyrroniumbromide)*obstruktiv*, *KOL*
T2DM	T90	or	A10(diabetes medicine) *sukkersyge*, *diabetes*
CVD	K74, K76^c^		

^a^The indicative text is in Danish and has not been translated as some indicative texts are only parts of the entire word and as such not translatable

^b^The reason for the large number of indicative text is misspellings by the GP when indicating the purpose of the prescription

^c^Diagnostic codes for ischemic heart diseases are transferred to the GP’s EPR system when the patients are discharged from the hospital following an angina or a stroke. ATC codes for prescribed medicine will not provide further information

Given the pre-existing diagnosis and/or treatment, Group 1 was excluded from the subsequent risk estimation and stratification into Group 2, 3, and 4.

### Stratification to group 2

Next, participants at risk of lifestyle-related disease were identified using three validated risk scores: the Chronic Obstructive Pulmonary Disease Population Screener (COPD-PS), the Danish Diabetes Risk model, and a modified Heartscore BMI score [30–32]. The COPD-PS uses an algorithm accounting for age, lifetime use of cigarettes, and smoking-related symptoms to identify at-risk patients who may benefit from a spirometry to test for COPD (Table 3) [31]. The Danish Diabetes Risk score is based on an algorithm that incorporates age, sex, BMI, known hypertension, leisure activity level, and family history of diabetes (Table 4) [30]. The modified Heartscore BMI score accounts for age, sex, body mass index (BMI), and smoking status (Table 5) [32].

**Table 3 Tab3:** Algorithm used for risk assessment of COPD

Characteristic		Score
During the past 4 weeks, how much of the time did you feel short of breath during every day activities? (e.g. Strolling, light gardening, cleaning, shopping etc.)	None of the time	0
	A little of the time	0
	Some of the time	1
	Most of the time	2
	All of the time	2
Do you ever cough up any “stuff,” such as mucus or phlegm?	No, never	0
	Only when I have a cold, pneumonia or sore throat	0
	Yes a few days a month	1
	Yes most days a week	1
	Yes every day	2

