Please select the answer that best describes you in the past 12 months. I do less than I used to because of my breathing problems.	Strongly disagree	0
	Disagree	0
	Unsure	0
	Agree	1
	Strongly agree	2
Have you smoked at least 100 cigarettes in your ENTIRE LIFE?	Yes	2
	No	0
Age	35–49 years	0
	50–59 years	1
	60–69 years	2
	+ 70 years	2

Cut off value: ≥5

**Table 4 Tab4:** Algorithm used for risk assessment of T2DM

Characteristic	Score
Sex	
Male	1
Female	0
Age	
40–44 years	0
45–49 years	1
50–54 years	2
55–59 years	3
60–69 years	4
BMI	
25–30 kg/m^2^	1
> 30 kg/m^2^	2
Known hypertension	
Yes	2
No	0
Primary recreational activity level during the past year:	
Participating in sports competitions or hard exercise several times a week	0
Active with sports at least three times a week or regularly perform heavy house or garden work	0
Strolling, cycling or other light exercise at least 4 h a week (including Sunday walks, light gardening and cycling/walking to work)	1
Reading, watching television or other sedentary jobs	1
Family history of diabetes (Family includes grandparents, parents, sibling and children):	
No family member with diabetes before the age of 70	0
One family member with diabetes before the age of 70	1
More than one family member with diabetes before the age of 70	2
Having had diabetes including gestational diabetes	
Yes	2
No	0

Cut off value: ≥5

**Table 5 Tab5:** Algorithms used for risk assessment of CVD

Age	BMI	Daily smoker
Female		
> 50 years	> 40 kg/m^2^	+
> 55 years	> 40 kg/m^2^	–
> 58 years	35–40 kg/m^2^	+
Male		
> 49 years	> 40 kg/m^2^	+
> 55 years	> 40 kg/m^2^	–
> 50 years	35–40 kg/m^2^	+
> 55 years	35–40 kg/m^2^	–
> 52 years	30–35 kg/m^2^	+
> 56 years	25–30 kg/m^2^	+

Consistent with the criteria of the four distinct stratification groups defined above, participants were categorized into Group 2 when one or more of the risk assessment algorithms indicated high likelihood of developing lifestyle-related disease (see Tables 3, 4 and 5).

### Stratification to group 3 and 4

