According to Eldridge et al., the study presented in this paper is a non-randomized pilot study. We chose a non-randomized design in order to examine the specific design features of a stepped wedge cluster randomized design for the full-scale randomized study. A stepped-wedge design is a type of cluster randomized design that meets the specific ethical and logistical demands of a delayed intervention performed in routine care where all participants will be offered the intervention [51]. The pilot resembles one cluster in a stepped wedge cluster randomized study, and will thus allow us to ascertain whether the intervention can be delivered during a three-month period, or if longer time is required to avoid carry-over effects [51]. In the event that more time is necessary to deliver the intervention, it will be difficult, if not impossible, to accurately determine the optimal duration of a cluster. This will likewise complicate the stepped wedge design. One way to compensate for incomplete knowledge on the optimal timeframe for the intervention may be to include a “wash out” period after every cluster allowing for any delay or lag in implementation before the next cluster is commenced [52]. The length of the “wash out” period can be estimated from the results of the pilot study.

We have randomly sampled 200 patients from each GP in order to have a source population that is representative of the target population. We have chosen to target people born between 1957 and 1986 to assess the risk of lifestyle-related disease and health-risk behavior at an age interval where changes in lifestyle will provide significant health effects and be cost-effective. To this end, we have chosen to assess variation in the proportion of patients at increased risk of lifestyle-related disease between baseline and the 12-week follow up as our primary health-related outcome. Further, given the fact that complex interventions, such as the one described here, usually have concurrent endpoints [23], we also collect data on a variety of other variables – both questionnaire- and register-based – related to both lifestyle and disease. We have yet to determine which of these endpoints to include in the full-scale randomized study.

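### The 12-week change in the at-risk proportion re-applies screening scores that contain age and known hypertension, so without a control group it mixes ageing and new detection with behaviour change

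*Protocol article*

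**What the plan says.** Under Strengths and limitations the authors write that "we have chosen to assess variation in the proportion of patients at increased risk of lifestyle-related disease between baseline and the 12-week follow up", and they call this their primary health-related outcome. Table 6 (Evaluation outcomes) defines it: "Risk of lifestyle related disease is based on the algorithms previously described in the methods section and in Tables 3, 4 and 5". The inputs named there are questionnaire Q2 at baseline and questionnaires Q6 and Q7 at the end of the study period.

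Under Stratification to group 2 the status is binary: "participants were categorized into Group 2 when one or more of the risk assessment algorithms indicated high likelihood of developing lifestyle-related disease". The items are:

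- **Table 3 (COPD, cut-off 5):** breathlessness, phlegm, breathing limitation over 12 months, age, and lifetime smoking ("Have you smoked at least 100 cigarettes in your ENTIRE LIFE").
- **Table 4 (T2DM, cut-off 5):** sex, age, BMI, known hypertension, family history, previous diabetes, and activity, worded as "Primary recreational activity level during the past year".
- **Table 5 (CVD):** combinations of sex, age, BMI and daily smoking.

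People with a recorded diagnosis or treatment were removed before any scoring: "Group 1 was excluded from the subsequent risk estimation and stratification into Group 2, 3, and 4". Table 7 lists known hypertension in Q2 and again in Q6 and Q7. Strengths and limitations classes the study as a non-randomised pilot, a type that it describes as having no control group.

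**The concern.** A score built to decide whom to screen is being used to measure change. Some of its items move for reasons unrelated to behaviour. Age bands rise with birthdays, and known hypertension turns to yes when someone is diagnosed. In a controlled comparison such drift would largely cancel. In a single-group before-after contrast it goes straight into the estimate.

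Baseline and follow-up also treat the same fact differently. Recorded hypertension takes a person out of scoring at baseline. At follow-up, read literally, newly known hypertension adds 2 points to the person's Table 4 score.

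At stake is how a small change is interpreted. The authors have not yet chosen the endpoints of the full-scale study, and this pilot is meant to inform that choice.

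**Working it through.** **Planning rates.** Sample size calculation gives 60% consent, 75% receiving a profile, 12% in Group 2 and 35% of those attending the GP. Its own figure, approximately 200 patients per GP for four checks, comes out as 4/(0.60 × 0.75 × 0.12 × 0.35) = 211.6. With 200 patients the yield is 3.78 checks, so this looks like rounding and does not affect the point. The article gives no expected size for the change in the at-risk proportion.

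**Possible effect through GP attendance.** Register based data gives a target population of 9,400.

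- Profiles: 9,400 × 0.60 × 0.75 = 4,230.
- Group 2: 4,230 × 0.12 = 508.
- Attenders: 508 × 0.35 = 178.
- Ceiling if every attender left the high-risk state: 0.12 × 0.35 = 4.2 points.
- If an assumed 10% did so: 0.42 points (about 18 people). If an assumed 30% did so: 1.26 points.

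**Birthdays.** The cohort spans 30 birth years (1957–1986) and follow-up is about 12 of 52 weeks from September 2016. Table 4 adds a point at 45, 50 and 55. Nobody turns 60 in 2016. With births spread evenly, (3/30) × (12/52) = 2.3% gain a Table 4 point. Table 3 adds a point at 50: (1/30) × (12/52) = 0.8%.

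A birthday changes status only if the non-age points are exactly one short. For Table 4 the drift is (1/30) × (12/52) × [P(non-age = 4) + P(non-age = 3) + P(non-age = 2)], for those turning 45, 50 and 55 respectively. The article gives no item frequencies, so these are assumed, with items independent:

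| Male | BMI 25–30 / >30 | Known hypertension | Activity point | Family: one / more | Previous diabetes | Flagged on Table 4 | Drift, points | Per 4,230 |
|---|---|---|---|---|---|---|---|---|
| 45% | 28% / 7% | 0% | 45% | 10% / 2% | 0% | 10.2% | 0.34 | 15 |
| 45% | 30% / 10% | 1% | 50% | 12% / 3% | 0.5% | 13.1% | 0.39 | 17 |
| 50% | 36% / 14% | 1% | 60% | 16% / 4% | 1% | 18.3% | 0.49 | 21 |
| 50% | 36% / 17% | 3% | 70% | 19% / 6% | 1.5% | 23.1% | 0.53 | 22 |
| 50% | 38% / 20% | 6% | 80% | 23% / 9% | 3% | 29.9% | 0.56 | 24 |

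The range is about 0.3 to 0.6 points. The first two rows lie closest to the planned 12%. With age held at baseline the drift is 0.

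**Precision, for scale.** The 95% half-width of the change is 1.96 × √[2 × 0.12 × 0.88 × (1 − ρ)/4,230]. For an assumed within-person correlation ρ of 0.9 it is 0.44 points, and for 0.8 it is 0.62. The drift is of that order.

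**New hypertension (+2 in Table 4).** Three cases follow from the text:

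1. A Group 2 member already counts as at risk, so a diagnosis cannot raise the proportion. It can mask improvement: someone at 5 who drops one BMI class reaches 4 and leaves the group, but 5 − 1 + 2 = 6 keeps that person in.
2. A person below all cut-offs with 3 or 4 points on Table 4 crosses to 5 or 6 and enters the group.
3. If the Group 1 exclusion is repeated at follow-up, a diagnosed Group 2 member leaves scoring and the proportion falls.

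**Responsiveness.** Items that can fall are 3 of 5 in Table 3, 2 of 7 in Table 4 and 2 of 4 in Table 5. That is 7 of 16, or 6 of 12 when each distinct item is counted once. Two of these, activity and breathing limitation, look back a year, and at week 12 some 40 of those 52 weeks precede baseline. Table 4 also gives light exercise and sedentary leisure the same point. Lifetime smoking in Table 3 cannot change on quitting, so cessation counts only in certain cells of Table 5.

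**The case against.** The strongest reply is that the article neither says that age is updated nor says that it is held. Age is not a listed item of Q2, Q6 or Q7, and such scoring rules often sit in an analysis plan that is not shown. This stands in part: the birthday figure is conditional on updating. But the article does fix the definition. It names the algorithms and the questionnaires and re-asks known hypertension, and literal application produces the mixing described.

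The magnitude can also be challenged, and most of this stands. The 10% success rate and the item frequencies are assumptions. The other 330 or so Group 2 members (508 − 178) also receive a profile and might improve. Group 1 is not scored, so the drift head counts shrink by its share, which the article does not give. People already positive on Table 3 or 5 cannot newly enter through Table 4. Scenarios flagging 18% or more sit poorly with the planned 12%. The comparison therefore shows similar order of size, not cancellation.

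A reader might infer that case-finding at the GP is scored as harm. The documents do not support that. The examination is offered to Group 2, who already count, and no clinical measurement is described for Group 3. Nor is a diabetes route established: previous diabetes is in Table 4 but not in the text description of that score or in the Table 7 lists for Q2, Q6 and Q7.

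Finally, this is a pilot, and the move to the full study rests on a steering committee's assessment of problems and solutions, not on the sign of this change. That limits the consequence but does not make the measure interpretable.

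**Conclusion.** The point holds in a limited form. Applied as written, the outcome mixes ageing and new detection with behaviour change in an uncontrolled before-after contrast. If age is updated, ageing alone moves the proportion by roughly 0.3 to 0.6 points under the assumed frequencies. That compares with 0.42 points for an assumed 10% success among attenders and a ceiling of 4.2 points from attenders.

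It would be tempting to conclude that the outcome is biased against the intervention, or that its sign will be wrong. Neither is shown. Ageing drift runs against the intervention, but repeating the Group 1 exclusion would push the other way, and selective response could too. It would also be too strong to say that most items cannot improve. That is true of Table 4 (5 of 7 cannot fall) and narrowly true when pooled (9 of 16), but untrue of Table 3 and exactly half by distinct item. Limited responsiveness over 12 weeks is the supportable statement.

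**What to change.** In the primary analysis, compute the follow-up score with age, sex, family history, lifetime smoking, known hypertension and any diabetes-history item held at their baseline values. Restrict it to participants scored at baseline, with Group 1 membership fixed at baseline, and pair within person. Update only BMI, daily smoking, activity and symptoms. Report new hypertension and diabetes diagnoses separately as detected cases, and keep the fully updated score as a sensitivity analysis. State where the previous-diabetes answer comes from, since Table 7 does not list it.

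The cost is analysis wording and slightly more analysis work. Table 7 already lists known hypertension, weight, smoking status, activity and COPD symptoms in Q2, Q6 and Q7. The change removes ageing and new-diagnosis drift from the primary contrast. It does not supply a control group, so other uncontrolled change remains, and it does not lengthen the 12-week window for the items with year-long recall.
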